#### Secondary analysis

The secondary analysis consists of the analysis of the global score values, and the comparison between the two study groups, of the patient questionnaires (with matching or adjustment for baseline anxiety values), the surgeons and the radiologists, using the Student’s t-test (/ non-parametric test) or the chi-square test (/ Fisher’s exact test), depending on the nature of the data. If a statistically significant difference between groups is found, a post-hoc analysis will follow on the questionnaire items, with multiple testing corrections.

Data on localization quality will also be analysed and compared between groups using one-tailed tests to ensure that they do not indicate an inferiority of the experimental device.

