### Study design

This is a single-center prospective trial designed to assess the interest in introducing the RFID localization technique at the Jean PERRIN center. Study design is presented in Fig. 1.

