**Fig. 1 Fig1:**
[figure not shown]
Design of the RFID study. The participation to the study will be proposed during a senology consultation to any patient requiring preoperative localization. The RFID tag and the hook wire will be respectively placed during the senology consultation and the day before the surgery. In the two groups, patients will fill out a Hospital Anxiety and Depression scale (HAD) questionnaire and then fill out a satisfaction questionnaire during the placement of the device (RFID tag or hook wire) and during the postoperative consultation at 1 month. Radiologists and surgeons will also fill out a questionnaire respectively after the localization and surgery procedures

Any patient requiring preoperative localization will receive a senology consultation and participation in the study could be proposed. A sequential inclusion in time will be performed: 20 inclusions in the gold-standard group, then 20 patients in the RFID group before repeating the inclusion scheme. Eighty patients will be enrolled.

The RFID tag or the hook wire will be respectively placed during the senology consultation and the day before or the day of the surgery. If the hook wire is placed the day before the surgery patients should stay in overnight.

As soon as they are included, patients will fill out a Hospital Anxiety and Depression scale (HAD) questionnaire to determine potential anxiety and depressive disorders.

The included patients will then fill out a satisfaction questionnaire in two steps:during the placement of the device (RFID tag or hook wire),during the postoperative consultation at 1 month

Radiologists and surgeons will fill out a questionnaire dedicated to them, respectively after the localization and surgery procedures.

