### Primary and secondary outcomes

The primary outcome is the patient’s satisfaction score with the preoperative localization technique, evaluated by a visual analog scale (see patient questionnaire).

Secondary outcomes are:the patient’s pain score in relation to the preoperative localization technique, evaluated by a visual analog scale (see “patient” questionnaire)the score of the patient’s stress in relation to the preoperative localization technique (see patient questionnaire)the scores of the precision and the operative comfort associated with the device (see surgeons questionnaire)the visualization of the needle on ultrasound, the visualization of the device on ultrasound and on stereotaxic, and the ease of insertion of the device (see radiologists questionnaire)the occurrence or not of a migration of the localization device, the histological data with the presence of the lesion in the surgical specimen, the invasion of the margins and therefore the resulting rate of revision surgery.

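### Surgeon and radiologist scores are compared without an operator term, so a shift in caseload between the time blocks could pass as a device effect

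*Protocol article*

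**What the plan says.** The Study design section describes the trial with the words "This is a single-center prospective trial". It includes patients in alternating blocks: "20 inclusions in the gold-standard group, then 20 patients in the RFID group before repeating the inclusion scheme". Patient selection gives each of the first two blocks about 3 months. Eighty patients are planned, 40 per device.

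Operator ratings are collected procedure by procedure: "Radiologists and surgeons will fill out a questionnaire dedicated to them, respectively after the localization and surgery procedures". For surgeons, the outcomes listed under Primary and secondary outcomes are "the scores of the precision and the operative comfort associated with the device (see surgeons questionnaire". Radiologists rate visualization and ease of insertion.

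The Secondary analysis section compares the global scores "of the patient questionnaires (with matching or adjustment for baseline anxiety values), the surgeons and the radiologists", and does so "using the Student’s t-test (/ non-parametric test) or the chi-square test (/ Fisher’s exact test), depending on the nature of the data". The bracket on baseline anxiety belongs to the patient questionnaires. No operator term, stratification or clustering method is named for the other two. A significant global result opens a further step: "If a statistically significant difference between groups is found, a post-hoc analysis will follow on the questionnaire items, with multiple testing corrections". The article does not say how many surgeons or radiologists take part, or how their cases fall across the blocks.

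**The concern.** The named tests treat the 80 ratings as independent. They are not, if one surgeon or radiologist rates many procedures: precision, comfort and ease of insertion are subjective, and each rater has a personal level. The raters also know which device they are rating.

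The exposure comes from the block allocation. Leave, rotas or turnover can change who does the work from one 3-month block to the next. Scheduling also differs by device, since Patient selection has the tag placed at least a week ahead and the wire the day before surgery, so different radiologists may be on duty. If a lenient rater does more of one device, the unadjusted comparison credits that leniency to the device.

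Two of the three secondary objectives in Table 1, surgeon and radiologist perception, rest on these tests. The global test is also the gate to the item-level analyses. Their multiplicity correction does not repair an error in the gate itself.

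**Working it through.** **The plan's own figure.** None is given for the operator ratings. The only sample-size figure, 30 per group at effect size ¾, concerns patient satisfaction. It reproduces approximately (28 by the normal formula, 29 by the exact t-test) and does not bear on this point.

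**Inputs.** From the protocol: 40 ratings per device, four alternating blocks of 20, two-sample test at 5% (two-sided assumed). Assumed, because the protocol gives neither: the number of operators K and the share of rating variance between operators (ICC, written ρ; total variance set to 1).

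**Mechanism.** Let p_k and q_k be operator k's share of cases under each device, with n = 40 per device and the same operators using both.

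- Actual variance of the difference in means: 2(1−ρ)/n + ρ Σ(p_k − q_k)².
- Variance that the t-test estimates, approximately: [2(1−ρ) + ρ{(1 − Σp_k²) + (1 − Σq_k²)}]/n.

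The operator term enters the actual variance only through differences in caseload share.

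*Perfect balance, K = 3, ρ = 0.3.* Actual: 2 × 0.7/40 = 0.035. Estimated: [1.4 + 0.3 × (2/3 + 2/3)]/40 = 1.8/40 = 0.045. Actual error: 2{1 − Φ(1.96 × √(0.045/0.035))} = 2{1 − Φ(2.22)} = 2.6%. Simulation gives 2.8%. The test is conservative.

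*Shifted mix, K = 3, ρ = 0.3, shares 1:2:3 against 3:2:1.* Σ(p_k − q_k)² = 2/9. Actual: 0.035 + 0.3 × 0.222 = 0.1017. Σp_k² = 14/36, so the estimate is [1.4 + 0.3 × 1.222]/40 = 0.0442. Actual error: 2{1 − Φ(1.96/√(0.1017/0.0442))} = 2{1 − Φ(1.29)} = 19.6%. Simulation gives 20.3%.

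**Simulation in the trial's block pattern.** No device effect; 80 ratings in four alternating blocks of 20; operator shares drawn afresh in each block from a Dirichlet distribution with concentration 100 (near-equal), 5 (moderate shift) or 1.5 (strong shift).

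| Test | Near-equal | Moderate | Strong |
|---|---|---|---|
| t-test, K = 3, ρ = 0.4 | 5.4% | 9.4% | 15.3% |
| t-test, K = 5, ρ = 0.2 | 5.9% | 6.8% | 8.8% |
| t-test, range over repeated runs, K = 3 or 5, ρ = 0.2 or 0.4 | about 5% | about 6-9% | about 9-16% |
| Operator fixed-effect model | about 5% | about 5% | about 5% |

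**Wider ranges.** With 3 to 8 operators and ρ from 0.05 to 0.30, the t-test error is 2.4-4.8% under perfect balance, 4.7-5.3% with random mixing, and 5.6-20% with the linear caseload shift used above.

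**Limit of the fixed-effect model.** If half of the operator variance reflects different reactions to the device, with K = 3 or 5 and ρ = 0.2 or 0.4, the error for inference beyond these operators is about 15-37% with the fixed-effect model and about 14-35% with the plain t-test. Adjustment then brings no gain for that wider inference.

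**The case against.** A reader might infer that repeated ratings by themselves make these p-values too small. The documents do not support that. When the same operators use both devices, a common rating level largely cancels, and the test is near 5% or conservative. Inflation needs a shift in operator mix or operators who react differently to the device, and the article reports neither. Alternating the blocks twice also offsets part of a steady staffing trend. The strong-shift setting is an extreme: with three operators, the busiest averages about 57% of a block. All of this stands, and it limits the size of the point.

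A reader might also infer that no operator identity is recorded. The questionnaires are in an additional file that is not shown, so this cannot be said.

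It can be objected further that covariates for secondary ratings belong in the full protocol or analysis plan. That would answer a complaint about missing detail. Here, however, the article names the tests and states an adjustment for the patient questionnaires only, so the analysis of operator scores is specified, and specified without regard to the rater.

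Finally, the consequences are limited: neither the primary outcome nor the sample size depends on these scores. That stands too.

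**Conclusion.** The point holds in a limited form. As written, the secondary tests of surgeon and radiologist scores offer no protection against a change in operator caseload between non-randomised blocks. Under the assumed 3 to 5 operators and ICC of 0.2 to 0.4, the nominal 5% error is about 5% with equal caseload, 6-9% with a moderate shift and 9-16% with a strong one. With perfect balance the test is conservative and loses power. The direction of error is therefore not fixed: the p-values can be wrong, but the documents do not show that they are inflated.

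Repeat raters are near certain with 80 procedures at one center. The number of operators, their variance and any caseload shift are assumptions. Nor is an operator term a full cure: it removes the effect of caseload mix, but does not support conclusions about other operators if reactions to the device differ. This is a worthwhile, inexpensive improvement to two secondary objectives and leaves the primary endpoint as it is.

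**What to change.** Replace the two-sample tests for surgeon and radiologist scores by a linear model (ordinal or logistic where the score requires it) of score on device, with operator as a fixed effect. Use a coded operator ID, and add one to the questionnaires if they do not already carry it. For patients already treated (64 were recruited when the article was written), the code would have to come from procedure records; whether those allow it is not stated.

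Report, for each operator, the number of ratings per device and the device difference. State that the conclusion applies to this center's operators.

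The cost is one data field, one model statement in the analysis plan, a few degrees of freedom and a narrower claim. No extra patients are needed.

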## Methods and study design

### Study objectives and outcomes

The primary objective of the RFID trial is to show the superiority of the RFID technique in terms of patient tolerance compared to the gold-standard (Table 1). It also aims to determine surgeons and radiologists perceptions of the RFID technique compared to gold-standard.

**Table 1 Tab1:** Primary and secondary objectives

**Primary objective**	• To show the RFID technique superiority in terms of patient tolerance compared to the gold-standard
**Secondary objectives**	• To compare the surgeon’s perception of the localization by RFID to the gold-standard
	• To compare the radiologist’s perception of the localization by RFID to the gold-standard
	• To demonstrate the non-inferiority of the RFID technique over the gold-standard in terms of performance

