### Patient selection

Inclusion and exclusion criteria are presented in Table 2. Patients over 18 year’s old requiring conservative surgery for an histologically proven non-palpable breast lesion (fibroadenomas, papillomas, atypical lesions and neoplasia) will be included.

**Table 2 Tab2:** Inclusion and non-inclusion criteria

**Inclusion criteria**	• Female over 18 years old • Requiring conservative surgery for an histologically proven non-palpable breast lesion (fibroadenomas, papillomas, atypical lesions and neoplasia) • Speaking and understanding French • Patients referred to senology for localization of non-palpable breast lesions by surgeons • Affiliated to the French Social Security System • Able to give informed consent
**Non-inclusion criteria**	• Multiple breast lesions • Patients with breast neoplasia during pregnancy • Persons deprived of liberty or under guardianship or incapable of giving consent • Refusal to participate

The estimated duration of patients’ enrolment is 1 year and 6 months: 80 patients will be enrolled and followed from the inclusion until one month after surgery. A sequential inclusion in time will be performed: 20 inclusions in the control group (gold-standard) during 3 months, then 20 patients in the “RFID group” for the following 3 months with an interim statistical analysis, before repeating the inclusion scheme. When patients consent to participate in the study, they are informed of the device they will receive. Patients of the hookwire group are convened the day before the surgery to install the device. Patients with the RFID tag have the device installation at least one week before their surgery.

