### Sample size calculation

The satisfaction score is a continuous score taking values between 0 and 10 points. To be able to show a minimum effect size of ¾, corresponding to a difference of about 23% of the overall score, for an estimated standard deviation of about 1.5 points, with a power of 80%, and considering a type I error rate of 5%, a number of 30 patients per group would be necessary. To take into account a rate of non-matchable patients of about 20%, as well as a rate of non-evaluable patients of about 10%, 40 patients will be included in each group, for a total of 80. Given the lack of preliminary data, and the uncertainty around the assumptions used for sample size calculation, an interim analysis will be performed after approximately half of the initially planned number of subjects has been included. The purpose of the interim analysis is to re-estimate the number of subjects needed based on the distribution of scores, in order to ensure sufficient statistical power of the study. Since no early ending is planned after the interim analysis, the alpha risk will not be adjusted, and the formal comparison between the two groups by hypothesis testing will be done only at the final analysis.

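### The objective to demonstrate non-inferiority of RFID performance is tested by a rule that is met when inferiority is merely not detected

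*Protocol article*

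**What the plan says.** The last secondary objective in Table 1 (Study objectives and outcomes) reads "To demonstrate the non-inferiority of the RFID technique over the gold-standard in terms of performance". The performance data, listed under Primary and secondary outcomes, are device migration, presence of the lesion in the specimen, and "the invasion of the margins and therefore the resulting rate of revision surgery".

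One sentence under Secondary analysis covers these data. They are to be "compared between groups using one-tailed tests to ensure that they do not indicate an inferiority of the experimental device". The article states no margin, no confidence-limit rule and no significance level for these tests.

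The planned 40 patients per group come from the satisfaction score alone (Sample size calculation), for "a minimum effect size of ¾". No expected rate is given for any performance outcome.

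**The concern.** The objective and the rule point in opposite directions. To demonstrate non-inferiority, one rejects the hypothesis that RFID is worse by at least a stated margin. The rule instead takes no difference as the null hypothesis and is satisfied when that null is not rejected. Absence of evidence of inferiority then counts as success.

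Two consequences follow. The probability of passing a device that is truly worse is a type II error, which the rule does not control. And that probability rises as the sample gets smaller, so a weaker trial supports the claim more easily.

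These outcomes bear on whether the device does its job in surgery. A favourable comfort result would be read next to a reassurance on performance that the rule cannot supply.

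**Working it through.** **The plan's own sample size.** Inputs from Sample size calculation: effect size 0.75, power 80%, type I error 5%. Normal approximation, two-sided: n = 2(1.960 + 0.842)²/0.75² = 27.9, so 28 per group. The exact t-test needs 29, and dividing by 0.955 for a rank test gives 29/0.955 = 30.4. The stated 30 is reproduced. Enrolment is then raised to 40 per group for losses. Nothing in this calculation concerns the performance outcomes.

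**How often the stated rule passes a worse device.** Inputs: 40 per arm (documents); one-sided 5% (assumption, since the level of the one-tailed tests is not stated); adverse-outcome rates (assumptions, shown as a range). Let X be the number of events with the wire, X ~ Bin(n, p_wire), and Y the number with RFID, Y ~ Bin(n, p_RFID). The pass probability is the sum of P(X = x)·P(Y = y) over all pairs (x, y) whose one-tailed p-value for RFID being worse is at least 0.05. The p-value comes from the uncorrected chi-square (pooled z) or from Fisher's exact test.

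| Wire → RFID | 40 per arm: chi-square / Fisher | 30 per arm: chi-square / Fisher |
|---|---|---|
| 5% → 10% | 77% / 91% | 81% / 95% |
| 10% → 20% | 65% / 76% | 69% / 84% |
| 15% → 25% | 70% / 78% | 74% / 85% |
| 15% → 30% | 51% / 60% | 58% / 72% |
| 5% → 20% | 32% / 46% | 41% / 64% |
| 20% → 40% | 36% / 46% | 48% / 58% |

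Every entry rises when the sample falls from 40 to 30 per arm. At 40 per arm and one-sided 2.5%, the pass rates are higher again: 75% / 84% for 10% → 20%, 63% / 72% for 15% → 30%, and 50% / 59% for 20% → 40%.

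**What a margin-based test would need.** With equal true rates p and margin m, SE = √(2p(1−p)/n), power = Φ(m/SE − z₁₋α), and for 80% power n = 2p(1−p)(z₁₋α + 0.842)²/m². Rates and margins are illustrative assumptions.

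- p = 15%, m = 10 points: SE at 40 per arm = √(0.255/40) = 0.080, and 0.10/SE = 1.25. Power = Φ(1.25 − 1.96) = 24% at one-sided 2.5%, or Φ(1.25 − 1.645) = 35% at 5%. Required n = 0.255 × 7.85/0.01, about 200 per arm, or 0.255 × 6.18/0.01, about 158.
- p = 5%, m = 15 points: required n = 0.095 × 7.85/0.0225 = 33.1, so 34 per arm at 2.5%, or 0.095 × 6.18/0.0225 = 26.1, so 27 at 5%. The normal approximation is generous at so low a rate. Exact enumeration with Newcombe limits at 40 per arm gives power of 71% (2.5%) or 82% (5%).

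**The case against.** The strongest reply is that the article condenses a longer approved protocol (version 10, Trial status), which is not shown. A margin may be stated there, and its absence from the article is not a fault. That stands, and this point does not rest on a missing margin. It rests on the rule the article does state. Reading the one-tailed test as a test against a shifted null does not rescue the sentence: such a test succeeds by rejecting inferiority, whereas here success is that inferiority is not indicated. It is also true that the sentence never says what will be declared. It is, however, the only analysis offered for the Table 1 objective.

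Three stronger readings are tempting, and the documents do not support them.

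- A reader might infer that a markedly worse device would usually pass. The documents give no rates. Under the assumed ones this holds for worsenings of 5 to 10 points and, narrowly, for 15% → 30%. It fails at one-sided 5% and 40 per arm for 5% → 20% and 20% → 40%.
- A reader might infer that 80 patients cannot support any non-inferiority claim. That depends on rate and margin. It is so for a 10-point margin at 15% rates. With a 15-point margin at 5% rates, the planned size is near or above what is needed.
- Because eligibility covers any "histologically proven non-palpable breast lesion (fibroadenomas, papillomas, atypical lesions and neoplasia) will be included", a reader might infer that benign lesions dilute the margin and re-operation comparison. The article fixes no denominator for those outcomes, pathology is collected (Data collections), and the case mix is unknown. An analysis set is commonly left to the full protocol or analysis plan, so no restriction to neoplasia is proposed here.

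**Conclusion.** The analysis sentence is wrong as written for the objective it serves. That conclusion needs no assumed rates: it follows from setting Table 1 beside the Secondary analysis section.

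The size of the problem does depend on assumptions. With 40 per arm and one-sided 5%, a device with a 5- or 10-point higher adverse rate (5% → 10%, 10% → 20%, 15% → 25%) passes in 65% to 91% of trials, depending on base rate and test. For larger differences the pass rate is about even or lower.

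Severity is should-fix. The objective is secondary, and neither the satisfaction comparison nor the sample size is affected.

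**What to change.** Replace the sentence on localization quality under Secondary analysis. Suggested wording: each performance outcome will be reported as the RFID-minus-hook-wire difference with a two-sided 95% confidence interval; non-inferiority will be concluded for an outcome only if the confidence bound on the unfavourable side excludes the margin for that outcome, stated and justified before the final analysis; a non-significant difference will not be taken as evidence of non-inferiority.

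If the full protocol already holds a margin, use that one. If there is none and none can be justified, reword the Table 1 objective as a descriptive comparison of performance, with no non-inferiority conclusion.

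The cost is a protocol amendment for a trial that already has ethics approval and had 64 of 80 patients recruited, and possibly the loss of a secondary claim. No extra patients or data are needed for the rewording. Formal group comparison is reserved for the final analysis, so the rule can still be settled before the comparison is made.

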### Trial status

As of this day, 64 patients have been recruited in the RFID trial. Participant recruitment began on 12 May 2021 and is expected to finish in November 2022. The approved protocol is version 10, 26/04/2022.

